## Abstract

During the pandemic, telemedicine and telehealth interventions have been leading in maintaining the continuity of care independently of patients’ physical location. However, the evidence available about the effectiveness of the telehealth approach for advanced cancer patients with chronic disease is limited. This interventional randomized pilot study aims to evaluate the acceptability of a daily telemonitoring of five vital parameters (heart rate, respiratory rate, blood oxygenation, blood pressure, and body temperature) using a medical device in advanced cancer patients with relevant cardiovascular and respiratory comorbidities assisted at home. The purpose of the current paper is to describe the design of the telemonitoring intervention in a home palliative and supportive care setting with the objective of optimizing the management of patients, improving both their quality of life and psychological status and the caregiver’s perceived care burden. This study may improve scientific knowledge regarding the impact of telemonitoring. Moreover, this intervention could foster continuous healthcare delivery and closer communication among the physician, patient and family, enabling the physician to have an updated overview of the clinical trajectory of the disease. Finally, the study may help family caregivers to maintain their habits and professional position and to limit financial consequences.

## 1. Introduction

The overloading of healthcare facilities and the necessity to prevent the risk of infection during the COVID-19 emergency have highlighted the need to implement significant changes in the organization and delivery of healthcare services, mainly when these are aimed at the most fragile segments of the population [1,2,3]. Within this context, telemedicine and telehealth interventions have acquired a leading role in maintaining the continuity of care independently from the physical location of cancer patients. However, the evidence available about the effectiveness of the telehealth approach for advanced cancer patients with chronic disease is limited [4,5].

Once the emergency was addressed, the attention to telemedicine interventions has remained high, although preliminary evidence is mixed and greatly variable depending on the type of disease [6].

As concerns patients with advanced cancer, a recent systematic review studied the degree of efficacy regarding the use of diverse web and technological devices, finding positive effects on quality of life (QOL) and psychosocial well-being [7]. However, the level of user satisfaction and engagement with these interventions remains unclear for advanced cancer patients. Recent research suggested that patient engagement can be considered a key factor in the effectiveness evaluation and a primary criterion in feasibility studies of telehealth approaches [8]. Therefore, there is a need to further investigate how advanced cancer patients engage with the wide range of existing telehealth devices to offer patient-centered care with a telemonitoring intervention personalized based on patients’ needs and clinical condition

Furthermore, scientific evidence is progressively underlining the potential role of telemedicine in home care protocols to assist an increasing number of advanced cancer patients with an efficient program of early palliative care [9,10]. The introduction of telemonitoring systems aims to facilitate more and more effective patient care, reducing both emergency room and hospital admissions and improving symptoms of distress, anxiety, and depression in patients and caregivers [11,12,13]. Self-monitoring also increases patients’ awareness by making them feel part of their care pathway and active contributors to their well-being [14,15,16].

Telemonitoring mainly uses medical devices to record parameters relating to the patient’s state of health or treatment progress. Once registered, the data are shared on a cloud platform and then viewed by the physician, who can intervene in real time in the event of clinically significant anomalies reported by the system.

Advanced cancer patients frequently have multiple comorbidities (i.e., respiratory distress, cardiovascular disease) due to disease progression and/or the side effects of therapies [17,18]. The presence of comorbidity makes this population even more fragile and needs fast and successful management of symptoms as well as integration and sharing among the specialists treating the patient, including oncologists and cardiologists [19]. Indeed, telemedicine and telemonitoring systems may support collaboration among health professionals, communication among health professionals and patients, as well as patient/family self-care in a patient empowerment mode [20].

The present study is embedded in the framework of the home palliative and supportive care program provided by the National Tumor Assistance (ANT) Foundation [21,22]. The mission of the ANT Foundation is to offer the possibility of spending the last period of life in one’s living environment, envisaging not only the physical effects of the disease but also the patient’s well-being and perceptions, with the main objective of preserving the quality of life of the patients and their families. To this aim, a multidisciplinary équipe of physicians, nurses, psychologists, and volunteers assists patients and their families at home during the different stages of the cancer disease, ensuring respect for their privacy, dignity, and autonomy.

Over the past few years, the ANT Foundation has introduced new technologies into its care space. Specifically, ANT introduced the use of virtual reality into clinical practice as a complementary therapy to improve the quality of life and the psychophysical symptoms experienced by the patients. The studies conducted by the ANT Foundation showed that the virtual reality intervention in oncological patients cared for at home had a positive impact on the short-term symptoms experienced by patients, inducing a decrease in pain, depression, anxiety, and shortness of breath and an improvement in well-being [23,24].

In addition, to meet the challenges imposed by the COVID-19 pandemic, ANT implemented audio and video call visits in order to continue to support patients and their families even at a distance. Specifically, Franchini et al. (2021) suggested that online visits should progressively be integrated into medical practice, although they should not replace visits in person [25].

This interventional study aims to evaluate the acceptability of the daily telemonitoring of five vital parameters (heart rate, respiratory rate, blood oxygenation, blood pressure, and body temperature) using a medical device in advanced cancer patients with relevant cardiovascular and respiratory comorbidities assisted at home.

The purpose of the current paper is to describe the design of this telemonitoring intervention in a home palliative and supportive care setting with the objective of optimizing the management of patients, taking into account not only their quality of life and psychological status but also the caregiver’s perceived care burden and satisfaction with the received care.

## 2. Materials and Methods

### 2.1. Study Design

The proposed investigation is a non-profit, single-center, interventional randomized pilot study with a medical device without drugs (Figure 1). The trial was registered at clinicaltrials.gov (accessed on 20 December 2022) (NCT05650814).

### 2.2. Setting

The home care model managed by the ANT Foundation employs a hospital-at-home approach in which a multidisciplinary team of physicians, nurses and psychologists, all trained in palliative and supportive care, works around-the-clock 24 h/7 days a week to assist cancer patients. The service is free for the patients, and it is offered in agreement with the National Health Service [21,22].

### 2.3. Study Population

Participants are advanced cancer patients assisted within the home care program of the ANT Foundation in the metropolitan area of Bologna (Italy). Inclusion and exclusion criteria can be found in Table 1.

### 2.4. Recruitment and Randomization

The investigator will be the ANT physician in charge with the home care of the patient. During the first visit, after verifying the inclusion and exclusion criteria, the investigator (ANT physician) will explain the study to the patient and caregiver and propose their participation. If they consent, after collecting informed consent for participation and personal data management, the physician will contact the Research Department of the ANT Foundation to include the dyad (patient and caregiver) in the study.

Participants will be randomly assigned by the Research Department staff to the ButterfLife group (25 patients) or the Control group (25 patients) by randomization using an Excel-generated random number set. Investigators that will run the statistical analysis will be blinded to the randomization procedure.

### 2.5. Procedures and Data Collection

The study will last eight weeks for each patient. On the first day (day 1), the investigator will ask the patient and his/her caregiver to answer the questionnaires.

For patients in the ButterfLife group, the investigator will deliver the ButterfLife device (Figure 2) at home and explain its use. ButterfLife is a medical device similar to a joypad, designed by the Unimore spinoff VST (Vital Signal in a Touch, VST Srl, Modena, Italy), which, through the use of three different sensors, a photoplethysmogram, electrocardiogram, and an infrared thermometer, simultaneously measures the five primary vital parameters defined by the World Health Organization in 90 s (heart rate, respiratory rate, blood oxygenation, blood pressure, and body temperature). The ButterfLife device is designed to make self-measurements and therefore requires no external intervention for measurements. To record these parameters, the patient has to place both hands on the device, and the data collected are immediately transmitted to a portal whose software (VST-FIVE) calculates the vital signs and allows visualization of the sharing with the doctor via a Wi-Fi network (https://my.vital.st/) (accessed on 22 December 2022). To guarantee a stable internet connection, a 4G LTE Wi-Fi Router (TP-Link, Hong Kong) will be provided at the patient’s home. In this way, it is possible to ensure the early detection of worsening and failure of the health state, enabling the timely activation of appropriate intervention in the home setting. The recorded data remains available for subsequent evaluation, long-term monitoring, and offline analysis. The patient is recommended to take the measurement once a day, preferably in the morning, and to repeat the measurement of parameters during the day if necessary. The investigator will leave a booklet containing simple written instructions with images explaining the use of ButterfLife. The doctor will check the data recorded by the patient every day (Supplementary Document 1) and the trend of the parameters over time by a graphical representation on the electronic medical record (Vitaever, Nethical Srl, Bologna, Italy) (https://www.vitaever.com/) (accessed on 20 December 2022). Daily telemonitoring will be conducted in addition to standard home care.

Patients in the control group will receive standard home care: visits will be planned according to the patient’s needs. In case of an unstable clinical condition, worsening of symptoms, and alteration of vital parameters, the patient can contact the physician or the nurse by phone, who will decide how to intervene.

### 2.6. Measures and Outcomes

The primary outcome of the study is the acceptability and the feasibility of the telemonitoring intervention measured as the percentage of eligible patients proposed for the study who agree to participate and the number of self-measurements/week per patient. Moreover, a questionnaire for evaluating the ButterfLife device (ease of use, difficulties encountered, and usefulness) was constructed based on several questionnaires already found in the literature [26] and will be administered to patients belonging to the ButterfLife group at the end of the telemonitoring period.

The secondary outcomes involving patients and caregivers are listed below.

The quality of life (QOL) of patients will be assessed by the EuroQoL-5D-3L questionnaire (EQ-5D-3L), Italian version [27,28], a generic instrument consisting of 2 distinct sections: patient’s subjective assessment of five dimensions of quality of life (mobility, self-care, daily activities, pain/discomfort, and anxiety/depression); each item has responses graded from 1 to 3, where level 1 indicates no problems and level 3 indicates extreme limitation. Assessment of the patient’s perceived health status will be made on a visual analogue scale (VAS) graded from 0 (the worst possible health status) to 100 (the best possible health status).The psychological status of the patient will be evaluated by the Depression Anxiety Stress Scales-21 (DASS-21), Italian version [29,30], a self-assessment scale to detect depression, anxiety and stress. The scale consists of 21 items, 7 for each emotional state, assessed on a 4-point Likert scale (from 0 = never to 3 = always).Care burden perceived by the caregiver will be assessed by the Caregiver Burden Inventory (CBI) [31], a questionnaire consisting of 24 questions on 5 domains (time-dependent care burden, developmental burden, physical burden, social burden, and emotional burden). Completion requires ticking the box from 0 to 4 (0 = not at all, 1 = slightly, 2 = moderately, 3 = quite a lot, 4 = very much) that best describes the current condition or personal impression of the caregiver. The total score ranges from 0 to 100, where 100 indicates the highest perceived caregiver burden.Satisfaction with care stated by the caregiver will be assessed through the Family Satisfaction with Advanced Cancer Care-2 questionnaire (FAMCARE-2), Italian version [32,33], a specific validated instrument to measure family members’ satisfaction with the care received from a palliative care team for their relative with advanced cancer. The FAMCARE-2 consists of 17 questions whose answers, on a 5-point ordinal score ranging from 1 (very dissatisfied) to 5 (very satisfied), cover 5 domains (management of symptoms and patient comfort, information provided, support to the family, and psychological assistance to the patient). The total FAMCARE-2 score can range from 17 to 85, where 85 represents the highest satisfaction with the care received.

The total monitoring time will be 8 weeks: at day 1, after 4 weeks (day 28), and 8 weeks (day 56), the administration of questionnaires to the patient and caregiver will be repeated (Table 2).

Moreover, a series of secondary outcomes will be evaluated on physicians, the ANT Foundation, and the National Health System:The acceptability and ease of use of the device will be assessed by a questionnaire directed to the physician.The number of scheduled, unscheduled, and on-call visits (doctor and nurse), as well as the number of phone calls and emergency phone calls received by the doctor and nurse, will be assessed.The number of admissions to the emergency room will be assessed.Hospitalization days will be assessed.

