### 2.10. Statistical Analysis

A statistical analysis will be conducted on the data after their anonymization. An investigator is in charge of anonymization and blinding to groups’ patient allocation. The anonymized and blinded data will be passed to the investigators in charge of data analysis. Anonymized data will be stored within the Research Department of the ANT Foundation in an ad hoc safe electronic database. The statistical analysis will be structured as follows:Descriptive analysis of the characteristics of the recruited subjects. The following parameters are shown as frequencies: age, sex, KPS, diagnosis, time since diagnosis, presence of metastases, symptoms, current therapies, and stage of the disease.Analysis of acceptability and feasibility: percentage of eligible patients proposed for the study who agree to participate, percentage of drop out from the study, number of measurements/week per patient, patient assessment of ease of use, difficulties encountered, and usefulness.The trend of secondary outcomes (QOL, psychological state, and caregiver care burden) over time (day 1, day 28 and day 56) will be analyzed using a general linear model for repeated measures.Comparison between the ButterfLife and Control groups: after analyzing the normality of the variables (Shapiro–Wilk test), the differences between the two groups for secondary outcomes (QOL, psychological state, caregiver care burden, caregiver satisfaction with the care received, number of scheduled visits, unscheduled visits, on-call visits, phone calls received by the doctor and nurse, number of visits to the emergency room, number of hospital admissions and hospitalization) will be analyzed with parametric (Student’s *t*-test) or non-parametric tests (Mann–Whitney test).

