We expect a significant level of engagement in terms of the number of self-measurements/week per patient, ease of use, difficulties experienced, and usefulness. In this feasibility study, engagement will be evaluated by some indicators as defined by Perski et al., 2017 (and echoed by Goodman et al., 2022), including the frequency and duration of measurements, depth of device use, and others [8,42].

Furthermore, this telemonitoring intervention may have a positive impact on the caregivers. Improving advanced cancer patients’ QOL and psychological symptomatology may relieve the care burden perceived by caregivers and enhance the family’s satisfaction with the care received from the healthcare team. Indeed, previous studies stated that the caregiver’s QOL is related to the patient’s [43], making clear that a possible strategy for enhancing the caregiver’s QOL is to improve the patient’s [44]. In addition, telemedicine may help family caregivers to maintain their personal habits and professional position and to limit financial consequences due to missed workdays required to accompany their loved ones to medical clinics or hospitals [45].

In the present setting, one of the motivations sustaining the advantages of telehealth implementation is the potential to lower home care costs, as well as to improve and expand access to healthcare services [45]. Telehealth could impact costs by relieving the healthcare team from some clinical activities, such as the monitoring of vital parameters at home and reducing travel and workload [45].

The evaluation of secondary outcomes, such as the intensity of doctor/nurse home visits, phone calls, hospital admissions, and hospitalization days, will return an indirect measure of the impact of this telemonitoring intervention in terms of costs and suitability of resources provided by home care services and the National Health System.

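### The weekly count of self-measurements in the primary outcome mixes daily adherence with same-day repeats, so it cannot by itself show whether daily telemonitoring was followed

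*Protocol article*

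**What the plan says.** The Introduction sets the aim: to "evaluate the acceptability of the daily telemonitoring of five vital parameters".

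Section 2.6 defines the primary outcome, acceptability and feasibility, by two quantities. One is "the percentage of eligible patients proposed for the study who agree to participate". The other is "the number of self-measurements/week per patient". A device questionnaire at the end of telemonitoring is added. Section 2.10 repeats the use measure in the same form, listing "number of measurements/week per patient, patient assessment of ease of use, difficulties encountered, and usefulness" next to the consent and drop-out percentages.

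Section 2.5 describes what patients are asked to do. The basic instruction reads: "The patient is recommended to take the measurement once a day, preferably in the morning". Extra readings on the same day are allowed as well, since the patient may also "repeat the measurement of parameters during the day if necessary". Each recording goes at once to a portal and remains available for later analysis.

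Section 3 says how the count will be read: "We expect a significant level of engagement in terms of the number of self-measurements/week per patient". It also mentions frequency, duration and depth of use as engagement indicators, but does not define them or make them part of the primary outcome.

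Nowhere does the article count days with a measurement, limit the count to one per day, or separate routine readings from repeats.

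**The concern.** The aim concerns a daily routine, and the natural question is on how many days the patient measured. The stated quantity answers a different one: how many times the patient used the device in a week. The two agree only if nobody repeats a measurement, and the instructions expressly allow repeats.

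A patient who measures several times on a few days and skips the rest can therefore score as high as one who measures every day. Because Section 3 treats the count as engagement, a high value would be reported as a good result whichever pattern produced it. What is at stake is the interpretation of one of the two quantities that make up the primary outcome, and hence what a later, larger study would assume about daily use.

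**Working it through.** The article gives no figure for this measure, so there is nothing to reproduce. The check has two parts.

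**1. Weekly patterns (no assumptions)**

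Input: one measurement a day (Section 2.5), which is 7 a week and 7 × 8 = 56 over the eight weeks.

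| Readings on days 1 to 7 | Weekly count | Days with at least one | Days covered |
|---|---|---|---|
| 1,1,1,1,1,1,1 | 7 | 7 | 100% |
| 3,2,2,0,0,0,0 | 7 | 3 | 3/7 = 43% |
| 4,3,0,0,0,0,0 | 7 | 2 | 2/7 = 29% |
| 1,1,1,1,0,0,0 | 4 | 4 | 4/7 = 57% |
| 2,2,2,2,2,2,2 | 14 | 7 | 100% |

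The first three rows share one count with coverage from 29% to 100%. The fourth row covers more days than the second or third but has a lower count, so the count can also rank patients in the wrong order.

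**2. How often this would happen (assumed rates)**

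The documents give neither a daily use probability nor a repeat rate. Assume that each day is used with probability p, independently, and that each day of use brings a Poisson number of extra readings with mean r.

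- Mean days used per week = 7p.
- Mean weekly count = 7p(1 + r). The count therefore exceeds the days used, on average, by the factor 1 + r.
- With D the number of days used, D ~ Binomial(7, p). The chance of a week with a count of at least 7 but at most 3 days used is the sum over D = 1, 2, 3 of P(D) × P(Poisson(D·r) ≥ 7 − D).

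For p = 0.5 (mean 3.5 days a week):

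| r | Mean weekly count | Weeks with count ≥ 7 and ≤ 3 days used |
|---|---|---|
| 0 | 3.5 | 0% |
| 0.25 | 4.4 | 0.2% |
| 0.5 | 5.3 | 1.9% |
| 1 | 7.0 | 10.5% |
| 1.5 | 8.8 | 21.0% |

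Worked line for r = 1: P(D = 3) = 0.2734 and P(Poisson(3) ≥ 4) = 0.3528; P(D = 2) = 0.1641 and P(Poisson(2) ≥ 5) = 0.0527; the term for D = 1 is negligible. The sum is 0.0965 + 0.0086 = 0.105.

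Other values of p:

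- At p = 0.7 and r = 0.5 the mean count is 7 × 0.7 × 1.5 = 7.35, above the recommended 7, with 30% of days missed. Weeks with a count of at least 7 and at most 3 days used are then only 0.6%.
- At p = 0.9 such weeks stay below 0.2% for every r in the table.

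**The case against.** **A condensed article may leave the counting rule to the full protocol or analysis plan.** This is fair for the summary statistic. It does not remove the point, because Sections 2.6 and 2.10 both name the quantity itself, and both name a count of measurements.

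**Repeats are part of the recommended use, so total use is a legitimate descriptive measure in a pilot.** This stands, and is why the count should be kept. It does not make the count a measure of daily adherence.

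**The distortion may be negligible.** This stands as a limit. With no repeats, the count equals the days used. At 0.25 to 0.5 repeats per day of use and 50% daily use, the misleading weeks are about 0.2% to 2%. The article also sets no threshold for full use; 7 a week is only what the recommendation implies.

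**Other planned information bears on acceptability.** This stands. The consent percentage, the drop-out percentage and the device questionnaire are unaffected. None of them shows on how many days an enrolled patient measured.

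A reader might infer three stronger things that the documents do not support:

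- *That the study cannot answer its acceptability question.* The limitation applies to one component, for the reasons just given.
- *That the plan mishandles hospital stays, death or early stopping.* It states no rule for these, so it states none wrongly. A patient who measures daily for two weeks and then stops averages 7 a week over active weeks or 14/8 = 1.75 over all eight, but neither averaging rule is in the article, and a week-by-week series would show the stop.
- *That a high count signals sicker patients or failed readings.* The article does not say why a repeat might be needed and does not mention failed readings. Whatever prompts a repeat, it raises the count without adding a day of use.

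**Conclusion.** The point holds for the use component of the primary outcome. As stated, the weekly count mixes adherence to a daily routine with same-day repeats, and equal counts can go with anything from 29% to 100% of days covered in the patterns shown. That possibility follows from the article alone.

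Its likely size does not. It rests on the repeat rate, which is not given, and on the independence and Poisson assumptions used above. It ranges from nothing without repeats to about a fifth of weeks at 1.5 repeats per day of use with 50% daily use. The change is worth making because a measure that matches the stated aim can be derived from data already held.

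**What to change.** Report as the main adherence measure the number and percentage of days with at least one transmitted measurement, out of the days on which the patient is alive, at home and within the 56-day period. Count days after the patient chooses to stop measuring as not measured. Keep the weekly count as stated, beside the new measure, as a description of total use, and show same-day repeats separately.

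The patient's measurement instructions do not change. Section 2.5 says that recordings are transmitted to the portal and kept, so no new recording by patients should be needed. Days at home can be worked out from the hospitalization data that Section 2.6 already plans.

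Costs: reported adherence may be lower than the weekly count would suggest. The Data Availability statement says recruitment is in progress, so the change touches a primary measure of a running, registered trial. It must be documented with its date and reason before analysis.
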